### 3 JUSTIFICATION

The implementation of Enhanced Recovery After Bariatric Surgery (ERABS) has significantly reduced length of hospital stay (LOS) with no significant influence on overall morbidity or specific complication rates [1]. Currently discharge on postoperative day (POD) 1 is considered normal. Potential benefits of earlier discharge are improved patient and health professional satisfaction, and reduced healthcare costs. It has been shown in the literature that outpatient gastric sleeve [2] and gastric bypass [3] can be performed safely and with a low complication rate.

In a previous study (TRICA study; NCT03923127) which is currently executed and will be closed before this study here (PEACH) will start (Last patient last visit expected in August 2020), 350 patients have been included and worn the Healthdot in hospital after standard bariatric and large abdominal surgery. For 39 of these 350 patients overall, gold standard vital sign measurements of heart rate and respiratory rate have been recorded by electrocardiogram (ECG) and capnography respectively and compared with the Healthdot measurements to determine accuracy of the Healthdot system. An interim analysis shows that the Healthdot has an average error of 0.67 beats per minute (bpm) for heart rate on an aggregated level with 88.9% of all measurements below a deviation of 3 bpm to the gold standard ECG measurement. Additionally, the average error of breathing rates is -0.37 breath per minute (brpm) and 93.5% of all measurements below a deviation of 3brpm compared to capnography [4]. These data show that the Healthdot provides accurate measurements in view of its intended use. The here described PEACH study is the next step to validate the clinical usefulness of the Healthdot system by modifying the recovery path of bariatric patients after standard surgery by sending them home on the same day of surgery and comparing the outcome to the current recovery path, meaning the patients stay in hospital at least one night.

The most important reason to keep the patient in the hospital for one day is the detection of short-term complications such as bleeding. A remote monitoring system would allow the monitoring of vitals signs

|                                                                                                                    |              |                         |                  |                    |

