| Anticipated adverse device effects                                                            | The only anticipated adverse device effect is an allergic reaction to the plaster used to locate the device on the skin of the patient. This is mitigated by excluding patients with known allergies to these kind of medical adhesives.                                                                                                                                                                                                                                                                 |
| Residual risks associated with investigational device [as identified in risk analysis report] | 
The residual risks associated with the devices and their potential interference with the clinical work flow have been identified, scored and mitigated. From the risk analysis it is concluded that the residual risks associated with the devices are acceptable.
 
The residual privacy risks associated with the study are that the devices with heart rate and respiratory rate data on it could come of and fall in the hands of unauthorized people.
                                   |
| Risks associated with participation in clinical investigation                                 | Risks for participating in this investigation have been identified, assessed and mitigated. The residual risks are detailed in the Risk management Summary Matrix and are all deemed acceptable. Though the patients undergo surgery with the associated risks of this procedure this is not part of the study and the study does not influence the surgery risks. Sending the patient home on the same day has been assessed in bariatric surgery in several studies and risks associated with this are |

|                                                                                                                    |              |                         |                  |                    |
|--------------------------------------------------------------------------------------------------------------------|--------------|-------------------------|------------------|--------------------|
| Title: Clinical Investigation Plan                                                                                 |              | Author: [name] |                  | Philips restricted |

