## Reportability

All adverse events shall be reported to the Study Manager. ADEs, SAEs, SADEs and USADEs shall be reported to the Q&R office as well ([[contact]](mailto:[contact])). The Director Q&R shall assess the ADEs, SAEs, SADEs and USADEs for reportability to Competent Authorities.

Gewijzigde v

|                                                                                                                    |              |                         |                  |                    |
|--------------------------------------------------------------------------------------------------------------------|--------------|-------------------------|------------------|--------------------|
| Title: Clinical Investigation Plan                                                                                 |              | Author: [name] |                  | Philips restricted |
| DocID: ICBE-2-36455                                                                                                | Version: 3.0 | Date: 2020-DEC-08       | Status: Approved | Page: 39 of 44     |
| This document is based on Philips Research Template: Clinical Investigation Plan, ID: QR-TEM-57, Date: 2019-Mar-21 |              |                         |                  |                    |

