## Reporting process

Reporting shall include the date of the adverse event, research subject ID#, description of the adverse event, treatment, resolution, and assessment of both the seriousness and the relationship to the investigational device and study procedures.

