### Foreseeable adverse events and anticipated adverse device effects

No anticipated adverse device effects have been identified. However, since the study described here aims at detecting deterioration of health in patients post surgery, the following adverse events not associated with this study but with surgery in general are expected:

- Bleeding
- Anemia
- Anastomotic leakage
- Infection: wound, abdominal, pneumonia, urinary tract
- Dehydration
- Delayed gastric emptying
- Thrombosis: cerebral or cardiac infarction, intestinal ischemia, lung embolism

According to the Inspectie voor de Gezondheidszorg (Aanmeldingsformulier klinisch onderzoek met medisch hulpmiddel, Bijlage E 2017-07-14) these adverse events even if considered serious are not reportable since they are expected and described here as long as they do not lead to the suspension or termination of the trial or result in a change of the investigational product.

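### Section 14 declares listed surgical complications unrelated to the study and, even if serious, not reportable, against its own reporting and relatedness rules

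*Protocol*

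**What the plan says.** Section 14 of the protocol contains two sets of rules that cover the same events.

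The general rules are in the parts headed Reportability, Reporting process and Timelines. "All adverse events shall be reported to the Study Manager", and "ADEs, SAEs, SADEs and USADEs shall be reported to the Q&R office as well". The Director Q&R then assesses these events for reporting to competent authorities. Each report must contain an "assessment of both the seriousness and the relationship to the investigational device and study procedures". In the Timelines table, the row for serious adverse events gives an ethics committee route and makes no exception for expected complications.

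The special rule is under Foreseeable adverse events and anticipated adverse device effects. It says that "the following adverse events not associated with this study but with surgery in general are expected". The list runs from bleeding, anemia and anastomotic leakage through infection, dehydration and delayed gastric emptying to thrombosis. Citing an inspectorate form, it continues that "these adverse events even if considered serious are not reportable since they are expected and described here", with the condition "as long as they do not lead to the suspension or termination of the trial or result in a change of the investigational product". No recipient is named.

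This subsection also states that no anticipated device effects have been identified. Section 4 states: "The only anticipated adverse device effect is an allergic reaction to the plaster".

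**The concern.** A serious bleed cannot be both an event that is reported and judged case by case for relation to study procedures and one that is unrelated and exempt before it occurs. Site staff who read only the special rule could leave out a report, or leave out the relatedness judgement, that the general rules require.

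This matters more here than in a study that only adds a sensor. The trial moves discharge from the day after surgery to the evening of surgery, and it asks whether that is safe. Section 3 gives the purpose of what is removed: "The most important reason to keep the patient in the hospital for one day is the detection of short-term complications such as bleeding". A bleed that is recognised late at home is a harm the trial is meant to assess. A rule that labels it unrelated in advance takes away the case-level judgement that would show whether early discharge contributed.

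**Working it through.** There is no figure to reproduce. The check follows one event through each rule and then tests the two possible meanings of the exemption.

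**Example event.** A patient in the outpatient group goes home on the evening of surgery, bleeds at home and is readmitted because of a serious deterioration in health. Section 14 counts a serious deterioration that results in hospitalization as a serious adverse event, so this event is serious.

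| Rule in Section 14 | What it requires for this event |
|---|---|
| Reportability | Report to the Study Manager and to the Q&R office; Director Q&R assesses reporting to authorities |
| Reporting process | Judge relation to the device and to study procedures |
| Timelines, serious adverse event row | Ethics committee route, no carve-out |
| Foreseeable adverse events | Bleeding is listed: not associated with the study, not reportable |

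**Is early discharge a study procedure?** Section 3 says that the surgery and the in-hospital care are standard and not study procedures. It also says that the study evaluates whether sending patients home on the day of surgery is safe. Section 4 discusses same-day discharge under the risks of participating in the investigation. The protocol thus treats the timing of discharge as something the study does to the patient. Its relation to an event is a proper question under Reporting process.

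**Reading A: not reportable to anyone.** The exemption then contradicts Reportability, Reporting process and the serious adverse event row in Timelines.

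**Reading B: not reportable to the competent authority only.** Reports to the Study Manager and the Q&R office continue. Two conflicts remain. The exemption settles in advance what Reportability assigns to the Director Q&R, and the statement that the events are not associated with the study settles the relatedness that Reporting process asks for in each report.

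**Does the condition on the exemption remove the conflict?** It ends the exemption only if events lead to suspension or termination of the trial or to a change of the product. A single serious bleed would not normally do so. A cluster would lose the exemption only once it had led to such action, which is late for a report whose purpose is to prompt it.

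**Device effects.** One subsection says that none is anticipated; Section 4 names an allergic reaction to the plaster. Both cannot stand.

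**The case against.** The strongest reply is that the exemption was meant for the competent authority alone. Its sentence opens with a citation of an inspectorate notification form, and Reportability uses the same term for reporting to competent authorities. On that reading nothing is withheld from the Study Manager or the Q&R office, and the listed events are exempt from one external report because they are expected after this surgery. The events are also observed elsewhere. They count in the 30-day composite where they meet its criteria, in the comparison of adverse events between groups and in the interim analysis, and Section 7 allows the study to be stopped for accumulating adverse events.

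Most of this stands. It is the more natural reading, and it shows that the events are not lost as outcome data. It does not dispose of the point, because the text does not state the limit and because Reading B still leaves two conflicts. Observation in the composite is also no substitute for a judgement of relatedness in each case.

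A reader might go further and infer that the harms of early discharge escape oversight altogether. The documents do not support that, for the reasons just given. Nor is anything concluded here about an independent safety committee. The table in Timelines has empty cells in the serious adverse event row, which may be merged cells lost in conversion, so only its ethics committee entry is relied on.

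**Conclusion.** The point holds as a contradiction within Section 14 that should be corrected. It affects case-level safety reporting and relatedness; it does not touch the primary analysis. On the broad reading the exemption cancels reports that the same section requires. On the narrow reading it still pre-judges relatedness for a harm under test and pre-empts the Director Q&R's assessment. The mismatch with Section 4 on device effects is smaller but plain.

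Two stronger inferences should be resisted. A reader might turn the 95% textbook-outcome rate in Section 7 into a number of exempt events. That rate counts every composite failure, including prolonged stay and mild complications, and the protocol does not say how many failures are serious, listed or first seen after discharge. A reader might also extend the link with the overnight stay to leakage and thrombosis. Section 3 names only bleeding, as an example, and speaks of detection, not causation.

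The conclusion rests on the wording alone. The cited inspectorate form is not part of the protocol, so its exact scope is unknown, and the sponsor should confirm it.

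**What to change.** Reconcile the reporting rules of Section 14 as follows.

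1. State that the exemption concerns only reporting to the competent authority and does not alter reporting to the Study Manager, the Q&R office or the ethics committee.
2. Delete the statement that the listed events are not associated with the study.
3. Require that relation to study procedures, including same-day discharge, is judged for each listed serious event in both groups, as Reporting process already asks, and state that the exemption does not apply to an event judged related. A separate rule for the outpatient group is not needed and would make reporting differ by arm.
4. Align the statement on anticipated device effects with Section 4.

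The cost is a protocol amendment and possibly a few more reports. The underlying data are already collected through adverse event documentation and the 30-day endpoint, and the sample size and analysis do not change.

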### Information regarding the Data Management Committee, if established

N/A

### Incidental Finding Reporting

An Incidental Finding is a finding concerning an individual research participant that has potential health or reproductive importance and is discovered in the course of conducting research but is beyond the aims of the study.

All incidental findings will be documented in a timely manner throughout the study. The report Incidental Finding Report Form (see ICBE SP) will be in the receipt of Philips Research Q&R Office within 7 business days of when the researcher first learns about the finding.

|                                                                                                                    |              |                         |                  |                    |
|--------------------------------------------------------------------------------------------------------------------|--------------|-------------------------|------------------|--------------------|
| Title: Clinical Investigation Plan                                                                                 |              | Author: [name] |                  | Philips restricted |
| DocID: ICBE-2-36455                                                                                                | Version: 3.0 | Date: 2020-DEC-08       | Status: Approved | Page: 41 of 44     |
| This document is based on Philips Research Template: Clinical Investigation Plan, ID: QR-TEM-57, Date: 2019-Mar-21 |              |                         |                  |                    |

## 15 INVESTIGATOR BROCHURE (IB)

For this study an Investigator Brochure is provided to the investigator. Acceptance of this document will be documented in writing by the respective investigator.

## 16 VULNERABLE POPULATION

According to ISO 14155, a vulnerable subject is an individual whose willingness to volunteer in a clinical study could be unduly influenced by the expectation, whether justified or not, of benefits associated with participation or of retaliatory response from senior members of a hierarchy in case of refusal to participate.

- ☒ This study includes live human participants from non-vulnerable populations
  - ☐ Children or viable neonate (birth to age 28 days)
  - ☐ Cognitively impaired
  - ☐ Pregnant women (except USA)
  - ☐ Fetuses
  - ☐ Neonates of uncertain viability or nonviable
  - ☐ Prisoners
  - ☐ Poor/uninsured
- ☒ Educationally disadvantaged (limited education, e.g., high school drop out)
- ☒ Students (including interns, residents, fellows)
- ☒ Minorities (includes migrants, refugees)
- ☒ Elderly (over age 65 years)
- ☐ Terminally ill
- ☒ Other (check box and specifically discuss below)

In this study adult patients will participate including patients which are educationally disadvantaged students, minorities and older than 65 years only in case they are able to understand the study procedures and are able to provide informed consent themselves and none of the exclusion and all inclusion criteria are fulfilled. Therefore, these are not considered as vulnerable population for this study.

|                                                                                                                    |              |                         |                  |                    |
|--------------------------------------------------------------------------------------------------------------------|--------------|-------------------------|------------------|--------------------|
| Title: Clinical Investigation Plan                                                                                 |              | Author: [name] |                  | Philips restricted |
| DocID: ICBE-2-36455                                                                                                | Version: 3.0 | Date: 2020-DEC-08       | Status: Approved | Page: 42 of 44     |
| This document is based on Philips Research Template: Clinical Investigation Plan, ID: QR-TEM-57, Date: 2019-Mar-21 |              |                         |                  |                    |

To minimize the potential dependency of the patient to the investigators, the investigator informing on the study and collecting consent will not be the same as the one performing the surgery.

## 17 SUSPENSION OR PREMATURE TERMINATION

In case the study is suspended or ended prematurely, the investigator will notify the accredited METC and the ICBE as well as the RA about the reasons for the suspension or premature termination.

The principal investigator or authorized designee shall inform the subjects of the reasons for resumption.

The following criteria and arrangements for suspension or premature termination of the whole clinical investigation or of the clinical investigation in one or more investigation sites apply:

- Non-compliance to obtain patient informed consent
- Non-compliance to the inclusion/exclusion criteria
- Failure to follow patients per scheduled visits
- Failure to submit data in a timely manner
- METC or RA suspension of the trial or of the center

In case of suspension or premature termination of the clinical investigation, the following requirements apply for subject follow-up.

- Sponsor will promptly inform the clinical investigators of the termination or suspension together with the reasons why this decision was taken. They must also inform the regulatory authority(ies) (as stated by the applicable regulatory requirements).
- The EC will be promptly informed and provided with the reasons(s) for termination or suspension by the sponsor or by the clinical investigator.
- The investigator will promptly inform the patients and their personal physicians and assure appropriate therapy and follow-up for the patients.
- In case of early termination the investigator agreement will be terminated.

If the investigator (or METC) terminates or suspends the investigation without prior agreement of the Sponsor:

- The investigator will promptly inform Sponsor and the METC, and provide a detailed written explanation of the termination or suspension.
- The investigator will inform the institution (as stated by applicable regulatory requirements).
- The investigator will promptly inform the patients and their personal physicians and assure appropriate therapy and follow-up for the patients.
- The sponsor will inform the regulatory authority(ies) (as stated by applicable regulatory requirements).

|                                                                                                                    |              |                         |                  |                    |
|--------------------------------------------------------------------------------------------------------------------|--------------|-------------------------|------------------|--------------------|
| Title: Clinical Investigation Plan                                                                                 |              | Author: [name] |                  | Philips restricted |
| DocID: ICBE-2-36455                                                                                                | Version: 3.0 | Date: 2020-DEC-08       | Status: Approved | Page: 43 of 44     |
| This document is based on Philips Research Template: Clinical Investigation Plan, ID: QR-TEM-57, Date: 2019-Mar-21 |              |                         |                  |                    |

## 18 PUBLICATION POLICY

It is planned to register this study in a public database like clinical trials.gov or Nederland trial register. All manuscripts, abstracts, or other presentations will be reviewed by the Sponsor prior to release. The detailed publication strategy is described in the eMTIC framework contract and the applicable Exhibit specific for this study between the Sponsor and the clinical site.

Authorship and attribution will comply with ICJME guidelines, and privacy of participants will be safeguarded.

